## Abstract

**Background:**

Recent non-randomized studies suggest that extended endoscopic mucosal resection (EMR) is equally effective in removing large rectal adenomas as transanal endoscopic microsurgery (TEM). If equally effective, EMR might be a more cost-effective approach as this strategy does not require expensive equipment, general anesthesia and hospital admission. Furthermore, EMR appears to be associated with fewer complications.

The aim of this study is to compare the cost-effectiveness and cost-utility of TEM and EMR for the resection of large rectal adenomas.

**Methods/design:**

Multicenter randomized trial among 15 hospitals in the Netherlands. Patients with a rectal adenoma ≥ 3 cm, located between 1–15 cm ab ano, will be randomized to a TEM- or EMR-treatment strategy. For TEM, patients will be treated under general anesthesia, adenomas will be dissected en-bloc by a full-thickness excision, and patients will be admitted to the hospital. For EMR, no or conscious sedation is used, lesions will be resected through the submucosal plane in a piecemeal fashion, and patients will be discharged from the hospital. Residual adenoma that is visible during the first surveillance endoscopy at 3 months will be removed endoscopically in both treatment strategies and is considered as part of the primary treatment.

Primary outcome measure is the proportion of patients with recurrence after 3 months. Secondary outcome measures are: 2) number of days not spent in hospital from initial treatment until 2 years afterwards; 3) major and minor morbidity; 4) disease specific and general quality of life; 5) anorectal function; 6) health care utilization and costs. A cost-effectiveness and cost-utility analysis of EMR against TEM for large rectal adenomas will be performed from a societal perspective with respectively the costs per recurrence free patient and the cost per quality adjusted life year as outcome measures.

Based on comparable recurrence rates for TEM and EMR of 3.3% and considering an upper-limit of 10% for EMR to be non-inferior (beta-error 0.2 and one-sided alpha-error 0.05), 89 patients are needed per group.

**Discussion:**

The TREND study is the first randomized trial evaluating whether TEM or EMR is more cost-effective for the treatment of large rectal adenomas.

**Trial registration number:**

(trialregister.nl) NTR1422

## Background

Rectal cancer is a common disease in the Netherlands with approximately 4,000 new cases and 2,000 deaths annually[1]. The incidence of rectal cancer increases with age, male sex and obesity, without ethnic preference [2-4]. In the pathogenesis, premalignant intraepithelial neoplasia that is located in a rectal adenoma, precedes the occurrence of invasive rectal cancer[5,6]. Early endoscopic detection and removal of rectal adenomas prevents the development of rectal cancer and is therefore the most reliable contributor to the 'cure' of this disease[7,8]. When rectal adenomas become large, however, standard endoscopic therapies like simple loop polypectomy or one-step endoscopic resection will be inadequate. Therefore, large rectal adenomas must be removed either surgically or by extended endoscopic mucosal resection (EMR)[9].

In 1984 a novel surgical approach for the resection of large rectal adenomas has been introduced in Germany: transanal endoscopic microsurgery (TEM)[10]. This procedure encompasses general anesthesia, the use of expensive specialized equipment, a full-thickness rectal wall excision and hospital admission[11,12]. Since its introduction, many surgical practices (including the Netherlands) have adopted TEM as the new standard therapy for large rectal adenomas[13,14]. Alongside the introduction and refinement of TEM for rectal adenomas, advanced endoscopic therapies like extended EMR have rapidly evolved[15,16]. For extended EMR no sedation, no sophisticated equipment and no hospital admission are required as opposed to TEM[9]. Furthermore, only the neoplastic mucosa is resected instead of the full-thickness rectal wall, having a potential benefit of fewer complications.

Supporters of the TEM technique praise the excellent exposure of the rectum and the minimal invasiveness, as opposed to conventional surgical techniques [17-19]. Besides, recurrence rates after TEM appear to be lower when compared to conventional surgical transanal excision[20]. The TEM technique has shown to be highly efficacious in several retrospective and prospective case series with reported recurrence rates of 0–19% and complication rates of 2–21% [21-41].

On the other hand, extended EMR has gained more and more support in the last few years, mainly due to good clinical results after EMR in the esophagus and stomach[42,43]. Endoscopic mucosal resection has also been described for the treatment of large colorectal adenomas, revealing recurrence rates of 0–9% and complication rates of only 0–9% [44-53]. In case adenomas can not be removed completely during one EMR attempt, repeat EMR for residual disease generally leads to an overall success rate of 96–100%. Recently, the first prospective study analyzing extended EMR for large rectal adenomas has been described, revealing a recurrence rate of 8% and complication rate of 8%[9]. In this study, all recurrences were detected during the first control endoscopy after 3 months; repeat EMR of residual disease led to an overall success rate of 98.4%.

Since the efficacy of extended EMR for large rectal adenomas appears to be comparable to TEM, we started a prospective registration of patients with large non-pedunculated rectal adenomas who were treated by EMR in the Academic Medical Center Amsterdam. Preliminary results of this study were published in abstract form, demonstrating that EMR is safe and effective for the resection of large rectal adenomas having an overall success rate so far of 100%[54].

Until now, TEM and EMR have never been formally compared, and no such comparative studies have been registered at this moment. Although selection bias inevitably exists in prospective and retrospective case series, the results of these studies suggest that both TEM and EMR have comparable recurrence rates. Even when recurrences occur after TEM or EMR, most of these can successfully be re-treated without the need for radical surgery. The literature furthermore suggests that EMR is associated with fewer complications, reduced hospital admission, and no general anesthesia is required for EMR, all of which are favorable in both patients' and societal perspective. These contrasts of the two procedures might well lead to differences in costs and quality of life. Therefore, we designed a multicenter randomized trial to compare TEM and EMR for the resection of large rectal adenomas. The main objective of this study will be a cost-effectiveness and cost-utility analysis of these two procedures.

## Methods/Design

### Hypothesis

Transanal endoscopic microsurgery and extended EMR are both effective treatments for large rectal adenomas with comparable recurrence rates. However, EMR does not require general/spinal anesthesia or hospital admission and may be associated with lower morbidity. Therefore, EMR may improve quality of life and reduce health care costs.

### Objective

The main objective of the proposed randomized study is to compare the cost-effectiveness and cost-utility of TEM and EMR for the removal of large rectal adenomas. For a cost-effectiveness and cost-utility analysis the following study aims are taken into consideration:

▪ Comparison of recurrence rates after removal of large rectal adenomas by TEM or EMR.

▪ Comparison of morbidity and mortality associated with both procedures, by counting the number of patients with complications and the number of days that patients are alive, outside the hospital and without recurrence.

▪ Comparison of general and disease specific quality of life of patients before and after treatment by TEM or EMR.

▪ Comparison of health care service costs, production loss, and out-of-pocket expenses for TEM and EMR.

### Design

This will be a multicenter randomized trial comparing TEM and EMR in patients with large rectal adenomas with respect to cost-effectiveness and safety (figure 1).

**Figure 1 F1:**
[figure not shown]
**Flow chart of TREND study; 15 Dutch centers will be participating in this multicenter randomized trial (R = randomization)**.

### Randomization

Patient data are entered into a computerized database and by means of an unchangeable computer generated number patients will be randomized to undergo TEM or EMR. Randomization will be stratified by whether patients have a primary adenoma or residual/recurrent disease after prior resection.

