### Informed consent procedure

Consecutive eligible patients will be recruited at the outpatient clinic in the participating centers by the involved physician (surgeon or gastroenterologist). Patients fulfilling the abovementioned inclusion criteria will be informed about the study by the physician. After written informed consent, patients will be allocated to either TEM or EMR by computerized block randomization with variable block size via the study website . The patient will subsequently be scheduled for therapy in the participating centre. Patients unable or refusing to provide informed consent will be treated according to current clinical practice.

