#### Additional outcome measures

(a) Complications: subdivided into procedural (during treatment) and delayed complications (after ending the procedure); and further subdivided into major (requiring additional surgery) and minor (requiring endoscopic or medical intervention) complications.

During admission patients will be monitored for complications. In case of same day discharge from the hospital patients will be called by telephone 1 day after the procedure whether adverse events have happened. Two weeks after the intervention, a research nurse will contact the patient by telephone again and ask for occurred complications.

(b) Generic and disease-specific health related quality of life will be measured at baseline, 2 weeks, 3 months, 6 months, 1 year and 2 year follow-up by the EQ-5D, SF-36, Wexner score (for incontinence) and COREFO questionnaires[62].

(c) Costs of TEM and EMR from a societal perspective, based on primary data (see economic evaluation section).

(d) Patient preferences regarding TEM or EMR will be measured at the end of follow-up by a structured questionnaire to enable a discrete choice experiment addressing the burden of care, burden of complications, prognostic uncertainties, and recurrence rates of both treatments.

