### Data-analysis

Since the main outcome of this study is the neoplasia recurrence rate, i.e. proportion of patients with recurrent disease, the Chi-square test will be used to compare the intervention groups (TEM versus EMR). Since the event of recurrence, and not time to recurrence, is the most important indicator for treatment failure, Kaplan Meier methods will not be used. The complication and mortality rates will be compared in the same manner. The number of days not spent in hospital as additional primary outcome measure will be compared by the Wilcoxon rank sum test.

Differences between the intervention groups in continuous outcome measures (e.g. Wexner incontinence scale, quality of life questionnaires) will be tested by the student's t-test or Wilcoxon rank sum test, where appropriate.

All analyses will be carried out primarily on an intention-to-treat basis.

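### The stated tests for the quality-of-life and anorectal function scores include neither the baseline score nor the randomisation stratum, an avoidable loss of precision on additional outcomes

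*Protocol article*

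**What the plan says.** Three parts of the protocol article bear on this.

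- **Allocation.** The Randomization section states: "Randomization will be stratified by whether patients have a primary adenoma or residual/recurrent disease after prior resection". The Informed consent procedure section adds that allocation is by "computerized block randomization with variable block size".
- **Measurement.** Under Additional outcome measures, item (b), the scores "will be measured at baseline, 2 weeks, 3 months, 6 months, 1 year and 2 year follow-up"; the instruments are EQ-5D, SF-36, Wexner and COREFO. Each instrument therefore has one baseline and five follow-up values.
- **Analysis.** The Data-analysis section names a test for each type of outcome. For recurrence, "the Chi-square test will be used to compare the intervention groups (TEM versus EMR". Next, "The complication and mortality rates will be compared in the same manner". Days not spent in hospital "will be compared by the Wilcoxon rank sum test". Continuous outcomes, with Wexner and the quality-of-life questionnaires as its examples, are tested by Student's "t-test or Wilcoxon rank sum test, where appropriate".

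No stratified test, covariate or baseline term is named. The section also does not say whether the score tests apply to follow-up values or to changes from baseline. The Objective section describes the quality-of-life aim as a comparison spanning the time before and the time after treatment.

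**The concern.** The tests are named outcome by outcome, so this is a stated choice and not a gap left for an analysis plan. The words about appropriateness govern only the choice between the t-test and the Wilcoxon test.

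A baseline value of the same score usually predicts the follow-up value. A two-sample test on follow-up scores discards that information, and any chance baseline difference between arms passes into the treatment comparison. A test on changes uses the baseline, but with a fixed weight that is in general not the most precise one. Either way, data that every patient is asked to supply are used less well than they could be. The Hypothesis section names quality of life as one place where EMR may do better, so these comparisons matter to how the trial is read even though they are not primary.

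**Working it through.** **The plan's own size.** Inputs from the Abstract and Sample size calculation: 3.3% recurrence in both arms, an upper limit of 10% for EMR (margin 6.7 points), one-sided alpha 0.05, power 80%.

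n per arm = 2 × 0.033 × 0.967 × (1.645 + 0.842)² / 0.067² = 87.9, so 88 against the stated 89. Then 2 × 89 = 178, and 178 / 0.97 = 183.5, so 184 as stated. The size reproduces without any adjustment, so nothing below alters it.

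**Scores.** Let rho be the correlation between baseline and follow-up score, with equal variances at both times. Relative to a follow-up-only test (variance 1), a change-score test has variance 2(1 − rho) and baseline adjustment (ANCOVA) has 1 − rho². Relative to the change-score test, ANCOVA therefore has (1 + rho)/2. The article gives no rho, so the values here are assumptions.

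| Assumed rho | Cut against follow-up-only test | Cut against change-score test | 89 per arm worth, against follow-up-only |
|---|---|---|---|
| 0.3 | 1 − 0.91 = 9% | 1 − 0.65 = 35% | 89/0.91 = 98 |
| 0.5 | 1 − 0.75 = 25% | 1 − 0.75 = 25% | 89/0.75 = 119 |
| 0.7 | 1 − 0.51 = 49% | 1 − 0.85 = 15% | 89/0.51 = 175 |

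With 89 per arm and two-sided 5%, the follow-up-only t-test has 80% power for (1.96 + 0.842) × √(2/89) = 0.42 SD. With ANCOVA, power for the same difference is 84%, 90% and 98% at the three values of rho. A simulation that also included a stratum effect (assumed 20% share, 0.3 SD effect) gave 83%, 89% and 97%, against 78–80% for the t-test.

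**Chance imbalance.** The standard error of a baseline difference between arms is √(2/89) = 0.15 SD, so differences up to 1.96 × 0.15 = 0.29 SD are ordinary. Such a difference shifts a follow-up-only comparison by rho × 0.29: about 0.15 SD at rho 0.5 and 0.21 SD at rho 0.7. That is 35% and 49% of the 0.42 SD detectable difference.

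**Recurrence.** With share s of residual/recurrent lesions, recurrence probabilities pa (primary) and pb (residual/recurrent), and overall p = 0.033, stratifying removes the fraction s(1 − s)(pb − pa)² / [p(1 − p)] of the variance. The article gives neither s nor the rate ratio, so both are assumed.

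- Example: s = 0.2 and rate ratio 5 give pa = 0.033/1.8 = 0.0183 and pb = 0.0917. The fraction is 0.16 × 0.0733² / 0.0319 = 2.7%.
- Over s from 0.1 to 0.5 and rate ratios from 1 to 5, the cut is 0–2.7%, and power moves from 80.4% to at most 81.4%.
- A rate ratio of 10 gives at most 6.9%, and power of about 83%.
- In simulation (s of 0.1 to 0.3, rate ratios 1 to 5), non-inferiority power was about 83% with or without stratification, differing by at most 0.2 points.
- Expected recurrences: 178 × 0.033 = 5.9 over two arms and two strata, so empty cells are likely.

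**The case against.** Several objections have force.

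- **A reader might infer that the plan ignores the baseline.** The text does not establish this. A t-test or Wilcoxon test on change scores would fit both the Data-analysis wording and the aim in the Objective section. The 49% figure applies only if follow-up scores alone are tested. Against change scores the gain at rho 0.7 is 15%. This stands, which is why both ranges are given.
- **A reader might infer that the primary comparison loses power or is invalid.** It does not and is not. Leaving out a stratification factor makes the comparison at worst slightly conservative, and the precision at stake is negligible.
- **A reader might infer that lesion history was judged prognostic.** The Randomization section gives no reason for stratifying and no expected effect.
- **Rank tests are a legitimate choice for bounded or skewed scales such as Wexner.** This stands. It argues for keeping a rank-based analysis alongside the model, not against using the baseline.
- **Model terms are commonly left to an analysis plan, and this is a condensed article.** This stands only in part, because the article does name the tests and a plan would have to override them.

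**Conclusion.** The point holds for the quality-of-life and function scores. Under either reading of the named tests, adjusting for the baseline score is more precise at every correlation examined: 9–49% less variance than a follow-up-only test and 15–35% less than a change-score test, for assumed correlations of 0.3 to 0.7. The size of the gain rests on that assumption and on similar variances at baseline and follow-up. That some gain exists depends on neither the exact correlation nor the reading chosen.

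For recurrence the point is one of consistency between randomisation and analysis, not of precision. Because the scores are additional outcomes, neither the 89 per group nor the non-inferiority conclusion is in question. Whether a chi-square test suits a non-inferiority aim is a separate matter and lends this point no weight.

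**What to change.** In the Data-analysis section:

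1. Make the main analysis of Wexner, COREFO, SF-36 and EQ-5D a linear repeated-measures model over the follow-up visits, adjusted for the baseline score and the randomisation stratum, with the arm difference and its confidence interval reported.
2. Keep the Wilcoxon test, or a rank-based ANCOVA, as a sensitivity analysis for skewed scores.
3. For recurrence, report a stratum-adjusted risk difference with its confidence limit (for example Mantel-Haenszel), so that the analysis follows the randomisation. State in advance that the unstratified estimate will be used if the strata are too sparse.

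If a separate analysis plan exists, it should carry the same wording. The cost is text only, since all the data are already to be collected and no patients or visits are added. Fixing this before outcome data are compared by arm also removes the open choice between follow-up scores and changes.

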### Blinding

Blinding of patients and physicians during treatment is unfeasible, since the two treatment strategies are highly different in nature and in associated care. Endoscopic follow-up for recurrence, however, will be performed by independent endoscopists who are blinded for treatment strategy (see also primary outcome measure).

### Study population

Patients are eligible for this trial when they meet the following inclusion criteria:

(1) Diagnosed with a large non-pedunculated rectal adenoma (sessile or flat) with a largest diameter of ≥ 3 cm (estimated by an opened biopsy forceps of 8 mm or an opened resection snare of 13, 20 or 30 mm).

(2) The lower border of the adenoma is located at ≥ 1 cm and ≤ 15 cm from the anal verge, respectively.

(3) Biopsies of the lesion, if taken, did not show invasion of neoplastic tissue in the submucosal layer on histopathological evaluation; only lesions with intraepithelial (low or high grade) or intramucosal neoplasia are suitable for inclusion.

(4) During flexible video endoscopy there are no signs of endoscopic suspicion for submucosal invasive cancer (Kudo pit pattern type V; excavated/depressed type morphology; fold convergence; or large smooth nodule > 1 cm in a flat lesion)[55,56].

(5) In case of doubt, endoscopic ultrasonography (EUS) of the rectal adenoma should exclude invasion into the submucosal layer and exclude pathological lymphadenopathy (lymph nodes > 1 cm). When pathological lymph nodes are present, fine needle aspiration will be performed to exclude lymph node metastasis.

(6) If not performed already, total colonoscopy will be done to detect and remove all synchronous colonic adenomas or cancers first. Cecal intubation must be confirmed by identification of the appendiceal orifice and ileocecal valve.

(7) The general health condition of the patient permits general/spinal anesthesia (ASA-classification I-III).

(8) Absence of non-correctable coagulopathy (international normalized ratio > 2, or platelet count < 90 × 10^9^/l).

(9) Patient age of 18 years or older.

### Participating centers

Fifteen Dutch hospitals of the TREND-study group, including four academic and eleven non-academic centers, will enroll patients.

### Intervention strategies

#### Transanal endoscopic microsurgery

TEM will be performed as described by Buess[12]. Under general/spinal anesthesia a specialized TEM rectoscope of 12 or 20 cm in length (Wolf GmbH Knittlingen or Storz GmbH Tuttlingen, Germany) is inserted within the rectum to assure proper visualization of the lesion. The rectoscope is fixed to the operating table by a supporting device, providing the opportunity to reposition the rectoscope during ongoing surgery. The rectal cavity is insufflated with CO_2 _by a combined endosurgical unit to achieve constant distension for appropriate visualization of the rectal adenoma. The combined endosurgical unit further regulates irrigation and suction, thereby maintaining a constant intra rectal pressure. With the use of a binocular stereoscopic eyepiece for three-dimensional view (Wolf GmbH only) or a forward oblique telescope (Storz GmbH) a magnified view is being created for visualization of the lesion. With various instruments (multifunctional TEM400 (Erbe Elektromedizin GmbH, Tubingen, Germany), Ultracision harmonic scalpel (Ethicon Endo-Surgery, Cincinnati, USA), needle diathermy, tissue handling forceps, needle holder, suction probe, injection needle, clip applicator) the adenoma will be dissected by means of an *en-bloc *full-thickness rectal wall excision until the perirectal fat. Postoperatively, patients will preserve a urinary catheter that will be removed at the first postoperative day. Patients are admitted to the hospital in accordance with current practice.

After 3 months a control flexible endoscopy will be performed. If presumed residual disease is seen, biopsies will be taken to confirm the presence of neoplasia by histology. Hereafter, the residual adenomatous tissue will be resected endoscopically by either EMR (if > 5 mm) or argon plasma coagulation (APC) (if < 5 mm). Any intervention by EMR/APC at 3 months is part of the TEM treatment strategy.

